## Abstract

**Introduction::**

Chemotherapy-induced peripheral neuropathy (CIPN) is a worldwide concern in patients receiving neurotoxic agents for cancer therapy. High tone external muscle stimulation is a promising therapeutic approach to alleviate symptoms of CIPN.

**Methods::**

This pilot study aims to investigate whether the application of home-based high-tone external muscle stimulation therapy (HTEMS) improves symptoms of CIPN. The trial is planned as a therapist- and assessor-blinded, 1:1 randomized controlled study. A total of 50 patients with chemotherapy-induced peripheral polyneuropathy will be included. All patients will perform therapy at home. Study participants will be allocated randomly to the HTEMS therapy (intervention group) or to the transcutaneous electrical nerve stimulation (TENS, control group), respectively, following a standardized therapy schedule. Compliance of participants can be verified by reading out the tool box. Outcomes will be evaluated at baseline and after 8 weeks of home-based therapy. The primary outcome includes improvement of CIPN according to the patient-reported EORTC QLQ-CIPN 20 questionnaire. Secondary outcomes are the patient-reported change in health-related quality of life and clinician-reported changes of vibration sensibility, tendon reflexes, temperature sensibility, perception of touch, and strength of the lower leg muscles. Further a safety- and process evaluation will be performed.

**Discussion::**

This pilot RCT aims to evaluate the impact of home-based HTEMS as compared to TENS in CIPN. There is a need for an effective treatment for CIPN and the results of this study are expected to possibly identify a novel and effective treatment strategy in the future.

## Introduction

1

The use of chemotherapy has led to prolonged remission and survival in numerous cancer diseases. Chemotherapeutic agents have negative side effects and some of them are long-lasting. One of the most common adverse side effects of taxanes, platins, or vinca alkaloids is chemotherapy-induced peripheral neuropathy (CIPN). Prevalence of CIPN was reported in 30% to 40% of patients treated with neurotoxic chemotherapy and may be transient or permanent.^[1,2]^ CIPN appears predominantly as sensory neuropathy and affects the peripheral parts of the extremities in a “stocking and glove” distribution. It often presents with symptoms like paresthesia and numbness or tingling, but pain and motor symptoms can occur as well. Symptoms of CIPN may lead to dose reduction or even early cessation of chemotherapy and therefore may affect tumor control and survival in cancer patients. Furthermore, CIPN impairs quality of life (QoL), functional capacity, and increases annual costs of health care.^[3]^ Several factors have been identified which affect the risk of developing CIPN like smoking, low creatinine clearance, preexisting neuropathy or genetic predisposition^[4]^; however, etiology and underlying mechanisms are still controversial.

Currently, no evidence-based treatment (drug or non-drug therapy) is available for CIPN. Several approaches to alleviate peripheral neuropathy have been proposed, but evidence showing a benefit of these procedures regarding clinically relevant endpoints is scarce.^[5]^ Treatment with antidepressants, antiepileptics, topical ketamine, acupuncture, or magnetic field therapy failed to show significant relief so far.^[6,7]^ Although some promising results have been reported regarding the effects of nutraceuticals in the prevention or treatment of CIPN (magnesium, calcium, vitamins E and B6, glutamine, glutathione, N-acetyl cysteine, omega-3 fatty acids, and alpha lipoic acid), none of the agents has reproducibly shown effectiveness; moreover, acetyl-l-carnitine used in a RCT for taxane-induced neuropathy even markedly deteriorated CIPN in the study group.^[8,9]^ So far, only duloxetine was found to provide a moderate effect after 5 weeks.^[10]^ Many patients with chronic CIPN are referred to physical and exercise therapy. A recent systematic review analyzed the effects of specific exercise protocols on CIPN symptoms such as balance control, physical function, and QoL. However, the evidence is limited due to small sample sizes, heterogeneity among investigations (eg, type of exercise and durations), and use of outcome assessment methods.^[11]^ Hence, there is a strong need to implement more effective treatment regimes in CIPN.

In general, electrical sensory interventions are used for pain relief, muscle stimulation, and generating deep warmth in different tissues. However, a recent Cochrane review concludes that the evidence for transcutaneous electrical nerve stimulation (TENS) to relieve neuropathic pain in adults is poor.^[12]^ On the contrary, treatment with high-tone external muscle stimulation (HTEMS or high-tone therapy) seems a promising approach in the therapy of CIPN. The application of HTEMS has been shown to be more effective than TENS in the therapy of diabetic peripheral neuropathy.^[13,14]^ Furthermore, HTEMS demonstrated improvement in pain, discomfort, sleep disturbance, and QoL in patients with end-stage renal disease due to uremic peripheral neuropathy.^[15,16]^ The primary objective of this pilot RCT is to determine the efficacy of HTEMS therapy in CIPN compared to TENS therapy. Secondary objectives are the evaluation of process and safety of home-based HTEMS in patients with chemotherapy-induced peripheral neuropathy. The intervention group will receive HTEMS and the control group will receive TENS therapy. This pilot study aims to increase the feasibility of a successful RCT since a pilot trial can help to prevent a discontinued RCT in many cases.^[17]^

## Objective

2

The primary objective is to evaluate the impact of home-based HTEMS in patients with chemotherapy-induced peripheral neuropathy compared to TENS. The primary outcome measure is the patient-reported EORTC QLQ-CIPN 20 questionnaire (Table 1).

**Table 1 T1:**

PICO research question of HTEMS trial.

Secondary objectives of this RCT are to evaluate the effectiveness of home-based high-tone therapy since a pilot study is useful to assure the feasibility of a future RCT:

Determination of acceptance of home-based electrotherapy (technical problems, user comfort)Evaluation of recruitment, enrolment, randomization, completion, adherence, and attrition (withdrawal, dropout) ratesEvaluation of eligibility of recruited participantsEvaluation of data collection instrumentsCollection of data on reasons for refusal to participate, reasons for nonadherence with the intervention and control therapy, and reasons for attrition

## Methods/Design

3

This is a single-blinded randomized controlled trial with an observation time of 8 weeks. The protocol has been written according to the Standard Protocol Items Recommendations for Interventional Trials (SPIRIT) Statement^[18]^ and will be reported according to the Consolidated Standards of Reporting Trials (CONSORT) Statement.^[19]^ The SPIRIT Checklist is provided in Additional file 1 and the SPIRIT Diagram is depicted in Figure 1.

**Figure 1 F1:**
[figure not shown]
SPIRIT guideline diagram.

### Setting

3.1

The HTEMS-CIPN trial will be conducted at the University Hospital Salzburg and the Paracelsus Medical University in Salzburg, Austria, from January 2019 to December 2020.

### Inclusion criteria

3.2

Age ≥18 yearsConfirmed invasive cancerEastern Co-operative Oncology Group performance score 0 to 1Completed neoadjuvant or adjuvant chemotherapy with a taxane or platinTreatment with neurotoxic agent 4 to 24 weeks before enrolmentClinical diagnosis of CIPN ≥Grade 1 according to Common Terminology Criteria for Adverse Events during or after completion of chemotherapyAbility to complete questionnaires with or without assistanceAbility to understand the study protocol, its requirements, risks, and discomfortsSigned informed consent form

### Exclusion criteria

3.3

Ongoing treatment with antitumor treatments with potential neurotoxic side effects (eg, platins, taxanes, vinca alkaloids, bortezomib, or thalidomide)Completed chemotherapy with neurotoxic side effects other than taxane or platinPreexisting clinically manifest peripheral neuropathy before initiation of chemotherapy (eg, caused by radiation or malignant plexopathy, lumbar or cervical radiculopathy, carpal tunnel syndrome, vitamin B12 deficiency, AIDS, monoclonal gammopathy, diabetes, heavy metal poisoning amyloidosis, syphilis, hyperthyroidism or hypothyroidism, inherited neuropathy, among others.)Peripheral arterial occlusive disease >Grade 1Skin conditions such as open sores preventing proper application of electrodesPatients with implantable medical electronic devices (eg, pacemaker, implantable cardioverter defibrillator, catheter, and so on.)Patients with reduced left ventricular ejection fraction (<55%) and/or history of myocardial infarction, cardiomyopathies, myocarditis or other myocardial diseasesPatients with cardiac arrhythmiaPatients with epilepsyPatients with febrile illnesses or acute infectious diseasesPregnancy

### Patient identification and recruitment

3.4

The recruitment period covers 13 months (September 2019 to October 2020).

The Trial Steering Committee will supervise patient recruitment to ensure sufficient sample size in a stepwise patient recruitment approach.

Potential participants will be identified using a standardized admission form at the department of medical Oncology. The oncologists perform a precheck of the inclusion and exclusion criteria, inform potential participants about the study, and hand out the informed consent. The inclusion and exclusion criteria will be verified and informed consent will be obtained by the responsible physician at the Institute of Physical Medicine and Rehabilitation (PMR).Baseline data collection and outcome assessment (clinical examination and patient questionnaire) will be performed at the Institute of PMR.Randomization procedure and group allocation will be performed at the Institute of General Practice, Family Medicine, and Preventive Medicine.Participants will be allocated to either the HTEMS or TENS group after completion of chemotherapy, respectively (consecutive sampling).Instruction about the use of devices (intervention delivery) will be provided by a medical engineer at the Institute of PMR.Participants are instructed to follow the treatment protocol as described in the section delivery of intervention.

Following strategies to fulfill the recruitment goal have been developed: presenting the study for staff members, trial fact sheets for staff members, close contact with oncologists responsible for the patient identification, regular reports on the progress of recruitment.

### Randomization

3.5

The random allocation sequence will be generated using the random number generator available online. To ensure balance in the sample size across groups, we will perform stratified block randomization (ratio 1:1, block size 4). Subjects will be stratified by treatment delivery, taxane, and platin. To ensure concealment of allocation, randomization by computerized sequence generation will be performed as soon as patient recruitment is completed. After baseline data and outcome assessment, participants will consecutively be randomly assigned to the intervention or the control group. Thus, neither patients nor the responsible physician will know about the allocation to the HTEMS or TENS group at the time of recruitment.

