#### Description and delivery of HTEMS

3.7.1

The primary aim of HTEMS is to activate the metabolism of the cells. HTEMS is based on the idea that not only active exercise such as sports improves the metabolism, but also “passive applications” in the form of external electrical muscle stimulation will have positive effects. In contrast to TENS therapy, HTEMS operates directly on the muscle in-depth, producing pleasant but intense and thus effective contractions. Additionally, HTEMS modulates amplitude and frequency simultaneously. The applied frequencies range continuously from 4.096 to 32.768 Hz. It is important to offer a broad spectrum of frequencies as different frequencies activate structures of different sizes. The electrical stimulation is applied by using conductive rubber electrodes. The electrodes are positioned proximally and distally on the lower limbs. During the treatment, the muscle is stimulated to contraction by intervals. One interval consists of 3-second ramp-up time (intensity rises), 3-second holding time (intensity maintained at maximum), and 3-second pause (no stimulation). HTEMS will be performed with a HiTOP 191 therapy device (gbo Medizintechnik, Rimbach, Germany), which is a 230 V power supply device. The first treatment is performed and supervised by a training therapist at the Institute of PMR. Frequency and amplitude (intensity) are adjusted according to the manufacturers’ instruction individually to a tolerable level causing muscle contraction so that neither pain nor discomfort is produced. The participant is educated for home-based therapy and the treatment should be used daily for 30 minutes at least 5 days per week for 8 weeks. No specific daily time points are given to avoid constraining patients or disturbing their individual rhythm. The intervention should be performed regularly at a time point adapted to the patient's daily routine. The therapy will start within 4 to 24 weeks after completed chemotherapy to reduce the effect of any known or unknown biases related to the treatment regime. Potential study participants will receive information about the study as soon as symptoms occur, with inclusion, randomization, and allocation occurring within 4 to 24 weeks after finishing chemotherapy. The intervention will last 8 weeks.

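### The Randomization section ties randomization to the end of recruitment, contradicting its own consecutive assignment and the 4-to-24-week window; the wording must be reconciled

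*Protocol article*

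**What the plan says.** Section 3.5 (Randomization) plans stratified block randomization ("ratio 1:1, block size 4"). As the means of concealing allocation it states that "randomization by computerized sequence generation will be performed as soon as patient recruitment is completed". The next sentence reads: "After baseline data and outcome assessment, participants will consecutively be randomly assigned to the intervention or the control group".

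Section 3.4 (Patient identification and recruitment) states: "The recruitment period covers 13 months", from September 2019 to October 2020. It describes consecutive allocation after chemotherapy, and places randomization and group allocation at the Institute of General Practice, Family Medicine, and Preventive Medicine. Verification of eligibility, consent, baseline assessment and device instruction all take place at the Institute of Physical Medicine and Rehabilitation (PMR).

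Section 3.7.1 has therapy starting 4 to 24 weeks after chemotherapy, with "inclusion, randomization, and allocation occurring within 4 to 24 weeks after finishing chemotherapy".

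Baseline data are collected soon after consent (section 3.9), and the primary endpoint is the change in the CIPN 20 score over the 8 weeks of intervention (section 3.19). Section 3.6 blinds examining physicians, outcome assessors and analysts, but not participants or device instructors.

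**The concern.** The sentence on timing fixes when randomization happens, and as written it cannot be followed together with the rest of the protocol. Staff who wait for recruitment to close would break the window in section 3.7.1 and the consecutive assignment in sections 3.4 and 3.5. Staff who allocate each patient after baseline would break the sentence itself. The reader also cannot tell when the sequence is created, or whether it is fixed before assignments begin.

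If the sentence were followed, the primary endpoint would suffer. An early patient's baseline would be more than a year old at the start of therapy. The Discussion (section 4) says that taxane neuropathy typically improves after chemotherapy stops, while oxaliplatin symptoms may worsen for months. A change score meant to cover 8 weeks would then carry a long stretch of natural drift.

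A lesser point arises only if allocation is rolling. The protocol discloses a single block size of 4, and the unblinded device instructors work at the institute that enrols. If past allocations became known there, some later ones could be deduced.

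**Working it through.** The protocol gives no figure on this point to reproduce; the sample of 50 was set by feasibility (section 3.18).

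**Timing, literal reading**

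Inputs: recruitment of 13 months (section 3.4); window of weeks 4 to 24, which is 24 − 4 = 20 weeks wide (section 3.7.1). Assumption: uniform accrual.

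1. Length of recruitment: 13 × 365.25 / 12 / 7 = 56.5 weeks.
2. A patient who enrols T weeks after chemotherapy has 24 − T weeks of window left. That patient is still inside at the close of recruitment only if enrolled in its last 24 − T weeks. The share inside is (24 − T) / 56.5.
3. Most favourable case, everyone enrolled at T = 4: 20 / 56.5 = 35.4%, or about 18 of 50 patients.
4. Entry uniform over weeks 4 to 24 (a further assumption): the mean of 24 − T is 10, so 10 / 56.5 = 17.7%, or about 9 of 50.
5. If September to October is counted as 14 calendar months (60.9 weeks), the shares are 20 / 60.9 = 33% and 10 / 60.9 = 16%.
6. The first patient enrolled would be 56.5 + 4 = 60.5 to 56.5 + 24 = 80.5 weeks past chemotherapy when randomized. Baseline to final assessment would span 56.5 + 8 = 64.5 weeks, not 8.

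**Block of 4, rolling reading**

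Assumption: every past allocation within the stratum, and the block size, are known to those who enrol.

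1. A 1:1 block of 4 has 6 equally likely sequences. In 2 of them (AABB, BBAA) the last two places are certain; in the other 4 only the last place is. Certain share: (2 × 2 + 4 × 1) / (6 × 4) = 8 / 24 = 33.3%.
2. Simulation of 50 patients in strata of 50, 25/25, 35/15 and 20/20/10 gives 15.3 to 16.0 certain assignments.
3. Always guessing the arm that is behind is right with probability 1/2, 2/3, 2/3 and 1 at the four places: 2.833 / 4 = 70.8%, against 50% by chance.
4. The same guess is right 75.0% of the time for blocks of 2 and 68.3% for blocks of 6. For equally likely blocks of 2, 4 and 6, weighted by length: (2 × 0.750 + 4 × 0.708 + 6 × 0.683) / 12 = 70.3%.

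This guess uses only running totals and needs no knowledge of block size, so mixing sizes barely changes it. What hidden sizes reduce is the share known with certainty; the amount depends on what staff know and was not computed.

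**The case against.** The strongest reply is that the sentence is a slip. Everything around it describes rolling allocation for each patient: the following sentence, the recruitment steps in section 3.4 and the window in section 3.7.1. The phrase may simply mean the completion of that patient's own recruitment. This stands as the likely intent. A reader might infer from the 35% and 18% that most patients will be treated outside the window, but the documents do not support that. The figures show only that the literal instruction is incompatible with the rest.

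Three other inferences also go too far:

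- The per-patient reading is not impossible for blocked randomization. Blocks can be generated progressively within a stratum, with the same distribution as a list made in advance. A prior list is good practice, not a logical necessity.
- Delay is not irrelevant to concealment. A sequence that does not yet exist cannot be foreseen at enrolment.
- The timing and block problems cannot both occur. If randomization waits for the end of recruitment, block size cannot affect concealment at enrolment. If allocation is rolling, the window conflict goes away.

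On the blocks, it is fair to say that randomization sits at a separate institute, that assessors and analysts are blinded, and that no section says instructors share allocations with the enrolling physician. The 33% and 71% are therefore ceilings. Calling the trial open would be imprecise, since section 3 labels it single-blinded.

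None of this removes the contradiction, because the sentence does not say that it means each patient's own recruitment.

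**Conclusion.** The concern holds as a contradiction in wording that must be reconciled, because it governs how randomization is carried out. Taken literally, section 3.5 would leave at most about 35% of patients inside the protocol's own window under uniform accrual, and about 18% if entry is also uniform over weeks 4 to 24. It would also detach the baseline from the 8-week change it is meant to anchor. Rolling allocation is the probable intent, and under it every patient can be allocated inside the window.

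The fixed block of 4 is a secondary and optional point that applies only under rolling allocation. Up to 33% of assignments would be certain if block size and all past allocations were known by stratum. The protocol shows that unblinded instructors and enrolment share an institute; it does not show that such disclosure would occur.

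**What to change.** In section 3.5, delete the phrase that ties randomization to completed recruitment. State instead that the stratified sequence is generated before the first enrolment and held at the Institute of General Practice, Family Medicine, and Preventive Medicine, and that each patient is assigned from it after that patient's consent and baseline assessment. Check that sections 3.4, 3.5 and 3.7.1 then describe the same order of events. The cost is a short text amendment, plus a list prepared in advance if none exists.

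Optionally, replace the single block of 4 with randomly varied sizes (for example 2, 4 and 6) that are not disclosed to PMR. The gain is fewer assignments known with certainty; the best-guess rate stays near 70%. The cost is a new list and slightly larger possible imbalance between arms.

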### Blinding

3.6

Physicians responsible for the clinical examinations and outcome assessment will be blinded. Due to the technical design of the intervention, participants and device instructors cannot be blinded. The analysts and outcome assessors will be kept blind to patient allocation.

### Intervention

3.7

#### Description and delivery of HTEMS

3.7.1

The primary aim of HTEMS is to activate the metabolism of the cells. HTEMS is based on the idea that not only active exercise such as sports improves the metabolism, but also “passive applications” in the form of external electrical muscle stimulation will have positive effects. In contrast to TENS therapy, HTEMS operates directly on the muscle in-depth, producing pleasant but intense and thus effective contractions. Additionally, HTEMS modulates amplitude and frequency simultaneously. The applied frequencies range continuously from 4.096 to 32.768 Hz. It is important to offer a broad spectrum of frequencies as different frequencies activate structures of different sizes. The electrical stimulation is applied by using conductive rubber electrodes. The electrodes are positioned proximally and distally on the lower limbs. During the treatment, the muscle is stimulated to contraction by intervals. One interval consists of 3-second ramp-up time (intensity rises), 3-second holding time (intensity maintained at maximum), and 3-second pause (no stimulation). HTEMS will be performed with a HiTOP 191 therapy device (gbo Medizintechnik, Rimbach, Germany), which is a 230 V power supply device. The first treatment is performed and supervised by a training therapist at the Institute of PMR. Frequency and amplitude (intensity) are adjusted according to the manufacturers’ instruction individually to a tolerable level causing muscle contraction so that neither pain nor discomfort is produced. The participant is educated for home-based therapy and the treatment should be used daily for 30 minutes at least 5 days per week for 8 weeks. No specific daily time points are given to avoid constraining patients or disturbing their individual rhythm. The intervention should be performed regularly at a time point adapted to the patient's daily routine. The therapy will start within 4 to 24 weeks after completed chemotherapy to reduce the effect of any known or unknown biases related to the treatment regime. Potential study participants will receive information about the study as soon as symptoms occur, with inclusion, randomization, and allocation occurring within 4 to 24 weeks after finishing chemotherapy. The intervention will last 8 weeks.

